### Outcomes

The primary outcome is risk of all-cause mortality at 56-days following enrolment. Secondary outcomes are: time to all-cause mortality; proportions of patients with (i) microbiologically confirmed and (ii) clinically diagnosed TB disease; time to TB diagnosis and commencement of TB treatment; proportions of patients receiving antimicrobials and ART; and (i) duration of hospital admission, (ii) cumulative incidence of hospital readmission, and (iii) cumulative incidence of loss to follow-up. Outcomes will be ascertained by patient interview and review of medical notes during in-patient admission, and patient interview for vital status at 56-days post enrolment. This will be supplemented with information from patients’ next of kin for those lost to follow-up.

Microbiologically confirmed TB is defined as at least one positive smear-microscopy, Xpert, or culture positive result on any specimen or a positive urine TB-LAM result. Clinically diagnosed TB is defined as having a compatible clinical illness or radiological disease and/or the decision of the responsible clinical team to commence TB treatment in the absence of any positive microbiological tests for TB.

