### Study procedures

After obtaining written informed consent from eligible patients, a study nurse will collect data at baseline to determine clinical history, including TB symptoms, past history of TB and HIV care, vital signs and nutritional and performance status. Venepuncture for haemoglobin concentration and CD4 cell count will be conducted and single sputum sample and up to 50mls of urine will be collected from all participants, irrespective of study arm. If sputum and/or urine samples cannot be spontaneously produced, participants will remain in the study but no further samples for TB investigation will be arranged by the study team. However, the responsible medical team will remain at liberty to arrange further TB investigations that are available as standard of care at the study hospital.

A randomisation list stratified by study site using computer generated random block size will be generated. Randomisation will occur at enrolment, but the study team will be masked to study arm allocation. When TB samples (sputum and/or urine) from participants arrive in the laboratory, the study laboratory technician will identify the allocated study arm by opening a sealed envelope marked with the unique participant ID, and determine which samples will be screened for TB. Urine from participants randomised to the standard of care arm will not be tested for TB and will be safely discarded. TB-LAM assays will be read by the laboratory technician and results will be deemed as positive using the grade 1 cut-off on the manufacturer’s reference card. 20 % of TB-LAM assays will read by a second, blinded reader for quality control.

TB screening tests will only be processed during office working hours on weekdays. Once the TB screening tests have been completed (anticipated to be within 24-48 h of sample collection), the results will be issued whilst maintaining masking of the study arm and responsible medical teams (reported as either ‘TB screening test positive’, ‘TB screening test negative’ or ‘TB screening test not done’). Rifampicin resistance results, when available, will also be communicated to the medical teams.

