The responsible medical team will receive training on how to interpret the screening tests, including estimated positive and negative predictive values of the screening algorithms in each study arm, and that a negative screening test does not ‘rule out’ TB. The responsible medical team will be at liberty to organise further TB investigations and commence TB treatment as clinically appropriate. Management of HIV will be as per local and national guidelines, including timing of ART initiation. Data on TB investigations, diagnoses (including if microbiologically confirmed or ‘empirical’) and treatment will be collected during follow-up.

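### Clinically diagnosed TB, as worded, can be met with no TB diagnosis and no treatment decision; the confirmed/clinical split also needs any-TB and treatment-started proportions beside it

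*Protocol article*

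**What the plan says.** The protocol article, Outcomes, lists among the secondary outcomes the "proportions of patients with (i) microbiologically confirmed and (ii) clinically diagnosed TB disease", and separately the times to TB diagnosis and to starting TB treatment.

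- **Confirmed TB** is "at least one positive smear-microscopy, Xpert, or culture positive result on any specimen or a positive urine TB-LAM result".
- **Clinically diagnosed TB** is "having a compatible clinical illness or radiological disease and/or the decision of the responsible clinical team to commence TB treatment". A patient with a positive microbiological result of any kind is excluded from it, so the two categories are mutually exclusive.

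Under Study procedures, study urine tests are confined to one arm: "Urine from participants randomised to the standard of care arm will not be tested for TB and will be safely discarded". In both arms "the responsible medical team will remain at liberty to arrange further TB investigations that are available as standard of care at the study hospital". The same section states: "Data on TB investigations, diagnoses (including if microbiologically confirmed or ‘empirical’) and treatment will be collected during follow-up".

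Under Statistical analysis, binary secondary outcomes are compared between arms by logistic regression, and times to event by Kaplan-Meier curves and Cox models. No proportion with any TB diagnosis and no proportion starting TB treatment is listed.

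**The concern.** The name of the outcome and its rule do not match. The name refers to a diagnosis, but the rule can be met by features of the patient alone. Who judges compatibility is not stated. The trial enrols HIV-positive medical admissions whatever their presentation (Study population), and the Background describes the clinical features of TB in HIV as non-specific. A non-specific criterion is thus applied to an unselected population.

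The consequence bears on the trial's rationale. The Background motivates the trial by TB that goes unrecognised before death. Under the written rule, an untreated and unrecognised TB patient with a compatible illness is scored as clinically diagnosed. The Discussion also names frequent empirical treatment as a possible reason why earlier Xpert trials showed no benefit. Clinically diagnosed TB is the listed proportion closest to empirical treatment, yet it does not require treatment.

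The second issue is interpretation. Because study urine tests move patients out of the clinical category in one arm only, neither proportion alone says whether more patients were diagnosed.

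**Working it through.** **1. The article's own figures.** Rationale for studies of clinical impact gives 139/427 = 32.6%, stated as 33%. The yield is 28% for sputum Xpert and 81% for the full set of tests, and 0.81/0.28 = 2.89, stated as almost three-fold. Both reproduce.

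**2. The definition, read as written.** Take a test-negative patient with a compatible illness, no TB diagnosis in the notes and no TB treatment.

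- Positive microbiological test: none, so the exclusion does not apply.
- Compatible clinical illness or radiological disease: met.
- Treatment decision: absent, but not required because of the and/or.

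The patient counts as clinically diagnosed.

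**3. When this starts to matter.** Let g be the share of test-negative patients with a compatible illness or radiology. The article gives no value.

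- Confirmed TB: 0.33 × 0.28 = 9.2% (standard of care) and 0.33 × 0.81 = 26.7% (intervention).
- Test-negative: 90.8% and 73.3%.
- TB left unconfirmed: 33 − 9.2 = 23.8% and 33 − 26.7 = 6.3%.

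The first limb alone labels g × 90.8% and g × 73.3% as clinical TB. That exceeds all unconfirmed TB once g passes 23.8/90.8 = 26% in the standard of care arm and 6.3/73.3 = 9% in the intervention arm. As assumed values only, g = 50% gives about 45% versus 37%, and g = 90% gives about 82% versus 66%.

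**4. The confirmed/clinical split.** This is a separate illustration, restricted to patients with TB and not to be added to step 3. Take 1300 per arm and equal true TB, so 0.33 × 1300 = 429 per arm. Confirmed TB is 429 × 0.28 = 120 versus 429 × 0.81 = 347, a difference of 33 × (0.81 − 0.28) = 17.5 points. Over the interval for prevalence (28–37%) it is 14.8 to 19.6 points.

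Let f be the share of unconfirmed TB that is labelled clinical, equal in both arms (assumed; no value in the article). The clinical difference is −f × 17.5 points and the any-TB difference is (1 − f) × 17.5 points.

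| f | Clinical TB, n (standard vs intervention) | Difference, points | Any TB, n (standard vs intervention) | Difference, points |
|---|---|---|---|---|
| 1 | 309 vs 82 | −17.5 | 429 vs 429 | 0 |
| 0.75 | 232 vs 61 | −13.1 | 352 vs 409 | +4.4 |
| 0.5 | 154 vs 41 | −8.7 | 275 vs 388 | +8.7 |
| 0.25 | 77 vs 20 | −4.4 | 197 vs 368 | +13.1 |
| 0 | 0 vs 0 | 0 | 120 vs 347 | +17.5 |

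The confirmed difference is +17.5 points in every row, so it cannot separate relabelling from new detection. The any-TB column can. The issues interact: a looser clinical definition pushes f towards 1.

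Both illustrations count study tests only and ignore false positives and tests ordered by the routine team.

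**The case against.** **The definition is a condensed sentence.** The term itself says diagnosed, outcomes come from interviews and medical notes, and diagnoses are recorded as confirmed or empirical. In practice a recorded diagnosis may well be the source, and the analysis plan, which is not shown, may say so. That is fair about likely conduct. But the article states a complete rule, and that rule does not ask for a recorded diagnosis. It also gives no dating rule, so an effect on time to TB diagnosis is conditional on the same definition being used there.

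**More confirmed TB is the purpose of the intervention.** This stands. A reader might infer that the confirmed-TB difference is an artefact, with nobody's diagnosis changed. That holds only at f = 1. The Background points away from it: in the pooled post-mortem studies nearly half of those with TB had died without the diagnosis having been made. At f = 0.5, half of the difference is new detection.

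**Treatment is already compared.** This also stands. A reader might infer that the plan cannot show whether testing changed who was treated. Time to starting TB treatment is a listed outcome, does not depend on the confirmed or clinical label, and its Kaplan-Meier curve shows the cumulative proportion treated.

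**Any TB is the sum of two reported categories.** True, but under the present wording that sum inherits the loose clinical category.

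**Conclusion.** The wording of clinically diagnosed TB should be corrected. As written, the proportion can measure compatible illness rather than diagnosis and can count missed TB as diagnosed. The number affected cannot be derived from the article. On its prevalence and yield figures, the first limb alone would outnumber all unconfirmed TB once more than about 26% (standard of care) or 9% (intervention) of test-negative patients had compatible features.

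The asymmetry in urine testing is a matter of interpretation, not an error in measuring yield. Confirmed TB would differ by about 17.5 points (14.8 to 19.6 over the prevalence interval), and the relabelled part runs from none to all of it with f. This assumes equal true TB in both arms and that the background study's yields carry over.

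The point is confined to secondary outcomes. The primary outcome of all-cause mortality at 56 days and the comparison of time to TB treatment are unaffected.

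**What to change.** 1. Define clinically diagnosed TB as no positive microbiological test **and** either a recorded clinical TB diagnosis or a decision by the responsible team to start TB treatment. Keep compatible clinical or radiological features as descriptors only.
2. State whether time to TB diagnosis uses this definition, and which recorded date counts.
3. Report by arm the proportion with any TB diagnosis (confirmed or clinical) and the proportion starting TB treatment.
4. Present the confirmed/clinical split as diagnostic yield, noting that study urine tests were run in the intervention arm only.

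The cost is outcome wording in the protocol and analysis plan and two further tabulations. Diagnoses, investigations and treatment are already collected, so no new data are needed and the sample size does not change.

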### Economic analysis

An economic analysis from a societal perspective will be undertaken to demonstrate the longer-term clinical and budgetary impact as well as the cost-effectiveness of the intervention; demonstrating economic feasibility and cost-effectiveness will be essential prior to implementation, should this screening intervention prove effective. Given the complexities of diagnosis and treatment of HIV/TB coinfection for patients requiring hospital admission, we will estimate health service costs based upon resource utilization of trial participants, inclusive of laboratory reagents and services, inpatient hospitalization days and outpatient visits, as well as drug costs. Trial-site specific costs will be collected on a limited cohort of 100 participants per site. We anticipate that, in the short term, costs of hospital admission are likely to account for a large proportion of health service provider expenditure; over the longer term, we expect increased survival related to the intervention will result in greater cumulative antiretroviral drug costs. Longer term cost-effectiveness will be estimated based on the Cost-Effectiveness of Preventing AIDS Complications-International (CEPAC-I) computer simulation model [29]. Model-based outcomes will include a short-term validation of trial results; that is, we will ensure that model results after 2 months of simulation accurately reflect trial outcomes of 56 days. Longer-term model results will include: 1-year and 5-year survival, TB-deaths averted, overall deaths averted and per person costs as well as life expectancy (LE) and lifetime costs. At each time horizon (1-year, 5-year and lifetime), the incremental cost-effectiveness of the intervention compared with the standard of care (Δ$/ΔLE, both discounted by 3 % per year) will be calculated. Model results will be examined in one-way and multi-way deterministic sensitivity analyses, examining influential parameters of interest (e.g. mean CD4 at presentation, TB screening test sensitivity/specificity and cost, active TB prevalence on admission). In addition to cost-effectiveness analyses, the budgetary impact of implementation and scale-up at 1- and 5- years of this intervention will be reported.

### Sample size justification

Sample size calculations were based upon unpublished data from the trial sites, which showed a mortality of HIV-positive medical in-patients of 21–23 % during hospital admission and are supported by subsequently published meta-analyses on hospitalised HIV-positive patients in Africa [2, 30]. We assumed that 56-day mortality would be 25–30 % in the standard of care arm and, based upon post-mortem prevalence of TB, we estimated 40–50 % of deaths in the standard of care arm would be TB-related.

The sensitivity of the intervention for diagnosing TB disease was assumed to be 80 % (a 3-fold increase in diagnostic yield compared to sputum alone) based upon a background study [14]. An observational study of early-initiation of TB treatment among HIV-positive smear-negative hospital in-patients observed a reduction in mortality at 2-months of 47 % in patients whose TB treatment was expedited by use of WHO-recommended diagnostic algorithm compared to standard practice [31]. Our study was powered to detect a 40–50 % reduction in TB-related mortality, and assuming half of deaths are TB related, this would equate to a 20–25 % reduction in all-cause mortality. Our sample size of 1300 patients per arm would provide 90 % power to detect a 25 % reduction in mortality and 80 % power to detect a 20 % reduction in mortality, assuming an all-cause mortality of 25 % in the ‘standard of care’ arm and a 2-sided type 1 error of 5 % and 10–15 % loss to follow-up. If the 56-day mortality was unexpectedly lower (20 %) in the standard of care arm, our sample size would still provide 80 % power to detect a 25 % reduction in all-cause mortality.

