### Rationale for studies of clinical impact

A study from South Africa intensively screened unselected HIV-positive hospital admissions to medical wards with comprehensive clinical sampling (sputum, blood, urine and other clinically relevant samples) [14]. Using mycobacterial liquid culture and/or Xpert, TB was diagnosed in 139/427 patients (33 % TB prevalence, 95 % CI 28–37 %). However, only 28 % of microbiologically confirmed TB in this study could have been diagnosed by Xpert testing of sputum alone. In contrast, 81 % of TB cases could have been diagnosed by Xpert testing of both sputum and urine, with additional TB-LAM testing of urine, and results are available within the first 24 h of hospital admission [14, 23]. Xpert is the best diagnostic test available in most high-burden settings and the WHO’s recommended initial TB test for HIV-positive patients. The use of this rapid, relatively low cost screening approach increased diagnostic yield by almost three-fold.

Despite this increase in diagnostic yield, there is no evidence that this urine-based screening strategy will impact mortality or clinical outcomes; it is recommended that impact be demonstrated before such interventions can be endorsed or implemented [24]. This is especially true, as numerous studies have noted that the replacement of sputum smear-microscopy with the more sensitive Xpert has failed to demonstrate any impact on clinical outcomes [25]. A recently published randomised controlled trial of adjunctive urine testing with the TB-LAM assay (the LAM RCT) in a selected population of hospitalised HIV-positive patients being investigated for TB demonstrated an absolute mortality reduction of 4 % (95%CI 1–7 %) and a relative reduction in mortality of 17 % (95%CI 4–27 %). These data support the potential for a urine-based screening approach to reduce mortality among unselected HIV-positive in-patients [26].

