### Study design

The trial is a pragmatic, individually randomised, multi-country clinical trial with two study arms with 1:1 allocation between arms (Fig. 1). HIV-positive patients randomised to the ‘standard of care’ arm will be screened for TB by testing sputum (if produced by spontaneous expectoration) using the Xpert assay. HIV-positive patients randomised to the intervention arm will, in addition to the standard of care, have a urine sample (if produced) tested for TB using the TB-LAM assay and, following concentration of 40–50mls of urine by centrifugation, the Xpert assay. Patients, the responsible medical team and study team will be masked to the study arm allocation (except for the study statistician, data managers and laboratory technicians). TB screening test results will be communicated to the medical teams responsible for clinical care of the patients (whilst maintaining masking to study arm allocation), but the clinical management decisions informed by the test results, including whether to commence TB treatment, will not be altered by the study team. Beyond collection of TB screening samples, running of assays and issuing of results, the study team will have no involvement in the clinical care of participants.

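### Power is understated for a 25% reduction, and the 20–25% target uses only the upper end of the plan's own TB share of deaths; at the lower end (16%) power is about 61–63%

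*Protocol article*

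**What the plan says.** The sample size justification rests on two steps.

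- **Effect size.** From post-mortem TB prevalence, "we estimated 40–50 % of deaths in the standard of care arm would be TB-related". The trial is said to be powered for a 40–50% cut in TB-related mortality and, "assuming half of deaths are TB related, this would equate to a 20–25 % reduction in all-cause mortality".
- **Power.** "Our sample size of 1300 patients per arm" "would provide 90 % power to detect a 25 % reduction in mortality", and 80% power for a 20% reduction. Both assume 25% control mortality, a two-sided 5% test and 10–15% loss to follow-up. If control mortality were 20%, "our sample size would still provide 80 % power to detect a 25 % reduction in all-cause mortality". The same section expects control mortality of 25–30%.

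The section does not say whether a reduction is in risk, odds or hazard. Under Outcomes, "The primary outcome is risk of all-cause mortality at 56-days following enrolment". Under Statistical analysis, the primary analysis counts patients lost before day 56 as not having died.

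**The concern.** Two things stand out. First, a trial that has only 80% power for 20% against 15%, or 90% for 25% against 18.75%, would need fewer evaluable patients than one with 80% power for 25% against 20%. The three figures therefore look as if they do not come from one calculation. Second, the TB share of deaths is first given as a range and then fixed at its upper limit, so the lower part of the implied effect range disappears before power is calculated.

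At stake is how the trial's sensitivity is understood. A reader would think the design weaker than it is for a 25% reduction. The same reader would not see that its own planning inputs allow an effect for which power is well below 80%.

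**Working it through.** **Inputs** (protocol article): 1300 per arm, "two study arms with 1:1 allocation between arms", two-sided 5%, loss 10–15%. Evaluable per arm: 1300 × 0.90 = 1170 and 1300 × 0.85 = 1105.

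**Formula.** Two proportions, normal approximation, pooled variance under the null. With p̄ the mean of p1 and p2, power = Φ{[(p1 − p2)√n − 1.96·√(2p̄(1 − p̄))] / √(p1(1 − p1) + p2(1 − p2))}. A reduction is read as a relative risk reduction, because the endpoint is a risk.

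**1. The plan's own figures.**

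Example, 25% vs 20% at n = 1170: (0.05 × 34.21 − 1.96 × 0.5906) / 0.5895 = 0.94, and Φ(0.94) = 82.6%.

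| Control vs intervention | Stated | 10% loss | 15% loss | Evaluable n per arm for stated power |
|---|---|---|---|---|
| 25% vs 18.75% | 90% | 95.6% | 94.5% | 917 |
| 25% vs 20% | 80% | 82.6% | 80.4% | 1094 |
| 20% vs 15% | 80% | 89.0% | 87.2% | 905 |

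The middle row reproduces: 1094 / 0.85 ≈ 1288, close to 1300, so it is the case that sets the sample size. The other two rows exceed the stated power by 4.5–5.6 and 7.2–9.0 points.

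**2. The same under the planned primary analysis.** If the lost count as alive, and loss d is equal in both arms and unrelated to death, both risks shrink by (1 − d) while n stays at 1300. At 10% loss, 25% vs 20% becomes 22.5% vs 18%.

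| Control vs intervention | 10% loss | 15% loss |
|---|---|---|
| 25% vs 18.75% | 95.1% | 93.6% |
| 25% vs 20% | 81.5% | 78.7% |
| 20% vs 15% | 88.3% | 86.1% |

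**3. Effect range from the plan's inputs.** All-cause reduction = TB share × reduction in TB deaths.

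- Share 50%: 0.50 × 0.40 = 20% to 0.50 × 0.50 = 25% (the stated range).
- Share 40%: 0.40 × 0.40 = 16% to 0.40 × 0.50 = 20%.
- Share 43%, the pooled post-mortem estimate given in the Background: 0.43 × 0.40 = 17.2% to 0.43 × 0.50 = 21.5%.

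**4. Power for a 16% reduction.**

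| Control vs intervention | Lost excluded, 10% / 15% loss | Lost counted as alive, 10% / 15% loss |
|---|---|---|
| 25% vs 21% | 63.3% / 60.8% | 62.0% / 58.9% |
| 30% vs 25.2% | 73.8% / 71.4% | 72.2% / 69.0% |
| 20% vs 16.8% | 51.5% / 49.2% | 50.6% / 48.0% |

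For scale, 80% power at 25% vs 21% would take 1737 evaluable per arm, or 1930–2044 enrolled per arm after 10–15% loss.

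**The case against.** The strongest reply is that nothing is overstated. Power statements are often rounded down, and as minimum values all three are met on the relative-risk scale. The only shortfall is about one point, for 25% vs 20% with 15% loss and the lost counted as alive. The case that sets the sample size reproduces. This reply stands, and it limits the first part to two imprecise figures on the cautious side.

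On the second part, the article says openly that it assumes half of deaths are TB-related, and 20–25% is a chosen target, not a promise to cover every combination of inputs. The 61–63% also combines three low ends: share, TB-mortality reduction and control risk. That is fair, and it is why the 30% row belongs beside it. It does not explain why a share given as 40–50% enters the conversion at 50% only, when the Background's pooled figure is 43%.

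Stronger readings are tempting but lack support:

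- **The three figures contradict each other or mix effect scales.** They differ only as exact values. The section never mentions hazards, so a mixture of scales is a guess.
- **The 80% sensitivity and the 47% mortality reduction multiply to a smaller effect.** The plan does no such multiplication. It takes the 40–50% cut in TB deaths directly, so any such product would be the reader's own model.
- **The 17% reduction in the earlier randomised trial of urine TB-LAM is the effect to plan for.** The Discussion describes a different population and a narrower intervention, and that trial's interval of 4–27% includes 20–25%.

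**Conclusion.** The point holds in two limited parts. The 90% and the second 80% are understated by about 5 and 7–9 points on the relative-risk scale, or about 4–5 and 6–8 points when the lost are counted as alive. The 20–25% target omits the lower end of the plan's own inputs. That end is 16%, where power is about 61–63% at 25% control mortality and 71–74% at 30%.

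This rests on three assumptions: reductions are relative reductions in risk; loss is 10–15% and equal between arms; and the normal approximation applies. A reader might infer that 2600 patients are too few. The documents do not support that: for the target that the plan declares, the sample size is adequate.

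**What to change.** Keep N = 2600 and revise the sample size paragraph.

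1. State that the reductions are relative risk reductions.
2. Recalculate power under the planned primary analysis (lost counted as alive, 10–15% loss): 94–95% for a 25% reduction from 25%, 79–82% for 20% from 25%, and 86–88% for 25% from 20%.
3. Replace the clause that fixes the TB share at one half. Say instead that, with 40–50% of deaths TB-related, a 40–50% cut in TB deaths equates to a 16–25% all-cause reduction. The clause must be replaced and not merely renumbered, because a share of one half does give 20–25%.
4. Add that, at 25% control mortality, power is about 80% or more only for reductions of 20% or more. For 16% it is about 59–62%, and 69–72% at 30% control mortality.

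The cost is wording only. No procedure changes. One stated range becomes less favourable, and the middle power figure may sit about a point below 80% at 15% loss.
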